#### Inclusion Criteria

Participants will be included in the trial if they are a co-parenting male-female couple aged 18 years or older, this is the first child for both parents, gestation is between 26 and 38 weeks at registration (couples registering before 26 weeks of gestation will be reminded by email to retake the screening survey when they reach the 26-week time point), and the pregnancy involves a single child. Participants must also be literate in English, have Internet and mobile phone access, and complete the baseline assessment. Both parents must be eligible for the couple to participate. Exclusion criteria are presented in Figure 1.

#### Screening and Baseline

Couples will register for the study by creating a website account for each user with email addresses and passwords. Registrants will then be individually emailed with a link to the screening survey, in which the trial information statement is provided. Participants will confirm that they have read and understood the statement, and that they consent to participate in the research before continuing. Participants will then complete the screening survey to confirm that they meet the study inclusion criteria. Eligible participants will be directed to the online baseline assessment survey, and both parents must complete the survey before the couple is randomly assigned to an intervention condition. Registrants who are not eligible for the study will still be able to access the *Babycare* program.

Reminder emails will be sent to registered participants on an automated schedule if they or their partner have not completed the screening survey three days post-registration, or the baseline survey three days post-screening. If the survey is still not complete 10 days post-registration, participants will be contacted by a research officer to assist with completion of the survey (if the couple gives ongoing consent to participate). If both individuals have not completed the baseline assessment four weeks after eligibility is confirmed, couples will be withdrawn from the study and offered access to the *Babycare* program. After completion of the baseline assessment and randomization, couples will be telephoned by a researcher (blind to treatment allocation) to welcome them to the study, collect postal address details, and provide the research team’s contact information.

#### Follow-Up Assessments

Follow-up assessments will be at 13 and 26 weeks post-baseline. For the purposes of these assessments, couples will be treated as individual participants and emailed an individualized online survey link. To maximize retention, participants will be reminded to complete the survey via scheduled emails. If the participant has not responded within two weeks of the due date, a researcher (blind to treatment allocation) will phone the participant, establish ongoing consent from the participant, and attempt to obtain the assessment over the phone. Participants will be offered an AUD $20 gift voucher (AUD $40 per couple) for completing each follow-up assessment.

#### Risk Management

Given the high frequency of perinatal distress, it is expected that some participants will experience distress during the study. Although the program focuses on well-being and does not specifically address depression, participants will be monitored for signs of elevated distress through their responses on the EPDS, and will be followed-up with according to the protocol outlined in Table 1. Researchers who make these calls will be trained in risk assessment procedures, will receive clinical supervision weekly to fortnightly, and will be blind to treatment allocation.

**Table 1 table1:** Risk management protocol after administration of the Edinburgh Postnatal Depression Scale.

Risk level	Risk cut-offs	Action
Low	Women: 0-9 total score Men: 0-5 total score AND 0 on Item 10	No action required.
Medium	Women: 10-12 total score Men: 6-8 total score OR 1 on Item 10	1. Email participant to organize a time to speak on the phone. Call within one week. 2. Re-administer the EPDS and check score against cut-offs. If now low risk, briefly discuss change between previous EPDS and current EPDS, and discuss what to do if situation worsens. Email referral information. If now high risk, follow protocol for high risk. If still medium risk, follow protocol below. 3. Discuss support options (ie, partner, family, friends). 4. Give support and referral information over the phone and by email: - PANDA (Post and Antenatal Depression Association) [name] http://www.panda.org.au/ - Lifeline [name] https://www.lifeline.org.au/Get-Help/ - Mensline [name] http://www.mensline.org.au/ - Family doctor - Psychologist www.psychology.org.au/FindaPsychologist/Default.aspx?ID=5911
High	Women: >13 total score Men: >9 total score OR 2 or 3 on Item 10	1. Email participant to organize a time to speak on the phone. Call same day. 2. Discuss support options (ie, partner, family, friends). 3. Give support and referral information over the phone and by email: - PANDA (Post and Antenatal Depression Association) [name] http://www.panda.org.au/ - Lifeline [name] https://www.lifeline.org.au/Get-Help/ - Mensline [name] http://www.mensline.org.au/ - Family doctor - Psychologist www.psychology.org.au/FindaPsychologist/Default.aspx?ID=5911 4. Assist participant to make a plan to access support, including immediate support if needed. 5. Arrange to speak again in one week, at which time the EPDS will be re-administered, and check score against cut-offs. If still high risk, remain engaged with participant until they are engaged with appropriate professional.

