## Results

Participant recruitment commenced March, 2015 and continued until October, 2015. Follow-up data collection has commenced and will be completed May, 2016 with results expected in July, 2016.

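### As printed, Table 1 assigns no risk band, and so no follow-up action, to a woman scoring 13 or a man scoring 9 on the EPDS with Item 10 = 0

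*Protocol article*

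**What the plan says.** The Risk Management section of the protocol article states that participants are monitored through their EPDS responses and "will be followed-up with according to the protocol outlined in Table 1". Table 1 then gives three bands:

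- Low: "Women: 0-9 total score Men: 0-5 total score AND 0 on Item 10". No action is needed.
- Medium: "Women: 10-12 total score Men: 6-8 total score OR 1 on Item 10". The participant is telephoned within one week and re-scored.
- High: "Women: >13 total score Men: >9 total score OR 2 or 3 on Item 10". The participant is telephoned the same day, helped to plan support, and re-scored a week later.

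Both action bands refer back to these cut-offs. In the Medium row the caller must "Re-administer the EPDS and check score against cut-offs". One branch covers a score that has become low; the others read "If now high risk, follow protocol for high risk. If still medium risk, follow protocol below". The last step of the High row reads "If still high risk, remain engaged with participant until they are engaged with appropriate professional".

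**The concern.** The Low and Medium bands adjoin each other: 9 to 10 for women, 5 to 6 for men. Medium and High do not. Medium ends at 12 and 8, while High as printed begins strictly above 13 and strictly above 9. One whole-number total per sex lies between them.

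This is a participant-safety matter. Table 1 is the only rule the article gives for acting on a raised EPDS score. Applied exactly, it requires a call for a woman at 12 and a same-day call for a woman at 14, and is silent for a woman at 13. The same holds for men at 8, 10 and 9. The people left out score higher than others whom the plan requires staff to contact.

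**Working it through.** **Coverage of the table.** The inputs are the three rows of Table 1. The total is taken as an integer from 0 to 30 (the maximum of 30 is an assumption) and Item 10 as an integer from 0 to 3. Every feasible combination was tested against each row, separately for women and men.

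| Total | Item 10 = 0 | Item 10 = 1 | Item 10 = 2 or 3 |
|---|---|---|---|
| Women, 12 | Medium | Medium | High (Medium also met) |
| Women, 13 | **none** | Medium | High |
| Women, 14 | High | High (Medium also met) | High |
| Men, 8 | Medium | Medium | High (Medium also met) |
| Men, 9 | **none** | Medium | High |
| Men, 10 | High | High (Medium also met) | High |

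Over the whole grid, the only combinations without a band are women (13, Item 10 = 0) and men (9, Item 10 = 0). With High read as ≥13 and ≥9, none is left for either sex.

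**Other sections.** Nothing else in the article assigns these scores. The EPDS cut-offs under Randomization (5 for fathers, 7 for mothers) define strata and do not govern risk follow-up.

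**Re-tests.** A person in the Medium band who re-scores 13 (woman) or 9 (man) with Item 10 = 0 is not low, not high as printed, and not still medium, so none of the three branches applies. A person in the High band who re-scores 13 or 9 does not meet the printed condition for continued engagement, but would meet it under ≥13 and ≥9.

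**Possible numbers.** The article gives no EPDS mean, SD or distribution, so this part rests on assumptions. Totals are taken as negative binomial with mean m and SD s, truncated at 30. The size parameter is r = m²/(s² − m) and the probability parameter is r/(r + m).

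- Mothers, mean 5 to 7, SD 4 to 4.7. At m = 5, s = 4: r = 25/(16 − 5) = 2.27 and P(13) = 0.0138. At m = 7, s = 4.7: r = 49/(22.09 − 7) = 3.25 and P(13) = 0.0276.
- Fathers, mean 3.5 to 4.5, SD 3.2 to 3.8. At m = 3.5, s = 3.2: r = 12.25/(10.24 − 3.5) = 1.82 and P(9) = 0.0230. At m = 4.5, s = 3.4: r = 20.25/(11.56 − 4.5) = 2.87 and P(9) = 0.0354.

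The planned 240 couples give 240 mothers and 240 fathers:

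- Lower end: 240 × 0.0138 + 240 × 0.0230 = 3.3 + 5.5 = 8.8
- Upper end: 240 × 0.0276 + 240 × 0.0354 = 6.6 + 8.5 = 15.1

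That is about 9 to 15 of 480 parents per administration. Some will score above 0 on Item 10 and so have a band. If that share is 0 to 30% (assumed), the lower end becomes 8.8 × 0.7 = 6.2, giving about 6 to 15 at baseline. If 70 to 100% complete a follow-up (assumed), the lower end becomes 6.2 × 0.7 = 4.3, giving about 4 to 15 at that follow-up.

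**The case against.** The strongest reply is that this is a lost symbol and not a decision. The article contains no greater-than-or-equal sign anywhere. Its four strict upper cut-offs (>13 and >9 in Table 1, >5 and >7 in the Randomization section) each skip exactly one integer, and each closes if read as ≥. That pattern suggests a systematic character problem in typesetting or extraction, and ≥13 and ≥9 is the likely intent. This stands as a probable explanation, but it cannot be confirmed from the text at hand. If the published table carries the strict sign, its rule is incomplete whatever the cause.

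Second, the callers are trained and clinically supervised, and nobody would sensibly treat a score above Medium as Low. They may well infer High. But a score has to be flagged before anyone calls, and a same-day safety trigger should not depend on inference.

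Third, the last step of the High row gives no branch for any re-test that is no longer high, so as printed a 13 is treated no differently from a 12. That is correct, and people being re-tested are already in telephone contact, so only their next step is undefined. The difference is that the likely intended cut-off would keep a 13 in the High band, and the printed one does not.

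Fourth, the counts above are of people at an exact score, not of people who missed follow-up. That is also correct. The second number would require knowing whether staff applied the strict sign literally, which the article does not say.

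**Conclusion.** The gap is real in the text as printed: exactly one combination per sex, a woman at 13 or a man at 9 with Item 10 = 0, has no band and no stated action. This follows from reading the table and needs no outside figure. The number affected is unknown. On the assumed distributions it is about 6 to 15 parents at baseline and 4 to 15 at a follow-up, and the conclusion does not depend on those counts.

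The cause may be a lost symbol, and staff may have acted as intended, so actual harm is not shown. It should still be fixed, because the table is the operative safety rule and the people it omits score above a band that already requires a call. Randomization, sample size, error rate and the efficacy analysis are untouched.

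**What to change.** Print the High row as ≥13 for women and ≥9 for men, with Item 10 of 2 or 3 unchanged, after the clinical team confirms that this was the intent. If the sign was lost in production, restore it. State that anyone meeting two rows takes the higher one, since a woman at 13 or a man at 9 with Item 10 = 1 would then meet both Medium and High.

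Apply the corrected cut-offs to the remaining assessments, including re-tests. There is still time on the article's own schedule: "Follow-up data collection has commenced and will be completed May, 2016". Baseline calls cannot be changed because recruitment has ended. So query the EPDS records already held for women at 13 and men at 9 with Item 10 = 0, and confirm that each was followed up.

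The cost is a one-line table correction and a short data query.

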#### Randomization

Allocations will be generated by the Goji program, a web-based research trials management system developed at Queensland University of Technology, Australia, by the same web developers who programmed the *Baby Steps* programs. When the researcher notifies Goji that a participating couple has completed their baseline assessment, Goji will allocate the participants to a research group, randomizing couples as a unit. Randomizations will be in permuted blocks, and stratified by scores on the EPDS: neither parent distressed (father <5; mother <7) versus either parent distressed (father >5; mother >7). These cut-off scores represent optimum screening levels for depressive or anxiety disorders in fathers and mothers [7]. After randomization, a couple’s access to the allocated program will be granted by a researcher not blind to treatment allocation, and participants will be notified by email that they are able to log into the online program through their registered account.

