#### Sample Size

A total of 240 couples (120 couples per group) will be recruited. A sample size of 240 will give a power of .80 for detecting a significant *Time* x *Condition interaction* (*P*<.05) over three occasions of measurement, with a small effect size of f=0.082 [50,51].

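### As printed, the EPDS randomisation strata are not exhaustive: a couple with one parent exactly on the cut-off and neither above it has no stratum

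*Protocol article*

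**What the plan says.** The Randomization section of the protocol article makes the couple the unit of allocation, with assignments generated by the Goji system. On method it says: "Randomizations will be in permuted blocks, and stratified by scores on the EPDS". The two strata are defined as "neither parent distressed (father <5; mother <7) versus either parent distressed (father >5; mother >7". The natural reading is that both conditions must hold for the first stratum and that either one suffices for the second.

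The section then explains the choice of 5 and 7: "These cut-off scores represent optimum screening levels for depressive or anxiety disorders in fathers and mothers". It does not say whether a parent scoring exactly at the cut-off counts as distressed.

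The Sample Size section gives the number to be allocated: "A total of 240 couples (120 couples per group) will be recruited".

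**The concern.** EPDS totals are whole numbers, as the bands in Table 1 of the article show. With strict inequalities on both sides of one integer, that integer belongs to neither side. A father at 5 is not below 5 and not above 5; the same holds for a mother at 7. Unless the partner is above the relevant cut-off, the couple fits neither definition.

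In stratified permuted-block randomisation the stratum decides which block list supplies a couple's assignment, so every couple needs one. The published rule cannot be applied to these couples, and Goji's handling of them cannot be derived from the text. Anyone rebuilding the stratification factor from baseline EPDS scores would have to guess on which side they fall.

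**Working it through.** **Which couples have no stratum.** Write F for the father's score and M for the mother's.

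- First stratum: F ≤ 4 and M ≤ 6.
- Second stratum: F ≥ 6 or M ≥ 8.
- Outside the second stratum: F ≤ 5 and M ≤ 7, which is 6 × 8 = 48 score pairs.
- Of these, inside the first stratum: 5 × 7 = 35 pairs.
- In neither: 48 − 35 = 13 pairs, namely F = 5 with M = 0-7 (8 pairs) and M = 7 with F = 0-4 (5 pairs).

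A father at 5 whose partner scores above 7, or a mother at 7 whose partner scores above 5, is still classified in the second stratum.

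**What share of couples that is.** The article gives no figure for this, and no EPDS mean, SD, distribution or within-couple correlation. The following inputs are therefore assumptions: negative-binomial scores; father mean 2-6 and SD 2.5-4; mother mean 4-8 and SD 3.5-5; correlation 0, 0.3 or 0.5 through a Gaussian copula. The formula is

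P(no stratum) = P(F ≤ 5, M ≤ 7) − P(F ≤ 4, M ≤ 6).

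| Father mean (SD) | Mother mean (SD) | Correlation | First stratum | No stratum | Second stratum | Couples of 240 with none |
|---|---|---|---|---|---|---|
| 3 (3) | 5 (4) | 0 | 0.547 | 0.103 | 0.350 | about 25 |
| 4 (3.5) | 6 (4.5) | 0 | 0.407 | 0.108 | 0.485 | about 26 |
| 4 (3.5) | 6 (4.5) | 0.3 | 0.451 | 0.101 | 0.449 | about 24 |
| 5 (4) | 7 (5) | 0 | 0.293 | 0.101 | 0.606 | about 24 |
| 2 (4), lowest in grid | 4 (5) | 0.5 | 0.716 | 0.047 | 0.236 | about 11 |
| 5 (2.5), highest in grid | 5 (3.5) | 0 | 0.331 | 0.158 | 0.511 | about 38 |

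Over the whole grid the share runs from 4.7% to 15.8%, with a median of 10.7%. In counts, 240 × 0.0474 = 11.4 and 240 × 0.1583 = 38.0.

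Counting every couple with a parent on a cut-off would overstate the gap. In the second row, P(F = 5) = 0.087 and P(M = 7) = 0.073, so 1 − 0.913 × 0.927 = 15.4% have at least one boundary parent, but only 10.8% have no stratum.

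**Whether the sample size is touched.** The plan's one design figure is its power: "A sample size of 240 will give a power of .80 for detecting a significant" Time × Condition interaction with f = 0.082 over three occasions. Assuming a correlation of 0.5 between occasions and sphericity (neither is stated), the noncentrality is 240 × 3 × 0.082² / (1 − 0.5) = 9.68. On 2 and 476 degrees of freedom this gives power 0.799, so .80 reproduces. The strata do not enter this calculation.

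**Effect of a corrected rule.** If each cut-off score goes to one side, whichever it is, no couple is left without a stratum.

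**The case against.** The strongest reply is that the fault lies in the printing. Table 1 has the same pattern: its Medium row ends at 12 for women and 8 for men, and its High row then begins above 13 and above 9, so totals of 13 and 9 fall in no band by total score. Two such gaps in one article suggest that a sign meaning at or above was lost. That is plausible and lowers confidence that the allocation code has the gap. The text cannot confirm it, however, and the published rule would still need correcting.

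A second reply is that little depends on the point. Recruitment ended in October 2015, a couple drawn from either block list is still randomised, and the Data Analyses section names no stratum covariate. This stands as a limit on the consequences. It does not make the rule usable as written. Nor is this a detail that an article leaves to a fuller document: the article states the exact rule.

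Three stronger readings are tempting and not supported:

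- A reader might infer a fixed share, such as one couple in nine. That is one value within the assumed range, and the article supplies no distribution from which to fix it.
- A reader might infer that Goji could not allocate these couples, or allocated them with bias. The article does not say how the boundary was coded.
- A reader might take the Low row of Table 1, "Women: 0-9 total score Men: 0-5 total score AND 0 on Item 10", as another instance. By total score that row has no gap, since the Medium row starts at 10 and 6, and it serves risk follow-up, not stratification.

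**Conclusion.** The point holds as a defect in the stated rule: 13 score pairs have no stratum, and nothing else in the article assigns them. That part rests on the printed text alone. The size, roughly 5-16% of couples or about 11-38 of 240, rests wholly on the assumed EPDS distributions and within-couple correlation, and should be quoted only as that range.

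The consequence is limited. The stratification factor is undefined for these couples, so balance within the strata as published cannot be checked and the factor cannot be reproduced from baseline data. The validity of random allocation and the sample size are not affected. It should be fixed, but it does not threaten the trial.

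**What to change.** - Read the inequality actually coded in Goji and restate the rule so that a father's score of 5 and a mother's score of 7 each fall on one stated side. The side should come from the code, because the article does not show which was meant.
- Confirm from the allocation records how couples with a parent on the cut-off were handled, and report it if it differs from the corrected rule.
- Use the stratum as allocated in Goji, not one rebuilt from the printed text, as a covariate in the mixed models.
- Reconcile the Medium and High bands of Table 1 separately. They govern risk follow-up and are a different matter from the strata.

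The cost is a check of one line of code and the allocation log, one corrected sentence and one model term. No new data are needed.

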#### Dropout

Couples will be randomized as a unit but may elect to withdraw individually or as a couple. An individual will be able to continue participating in the trial if their partner withdraws, and this will not have any effect on their participation in the trial.

#### Sample Size

A total of 240 couples (120 couples per group) will be recruited. A sample size of 240 will give a power of .80 for detecting a significant *Time* x *Condition interaction* (*P*<.05) over three occasions of measurement, with a small effect size of f=0.082 [50,51].

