### Hypotheses

It is predicted that participants receiving the *Well-being* program will show lower levels of distress and a higher level of quality of life at 13 and 26 weeks post-baseline, compared to participants receiving the *Babycare* program. In addition, couple relationship satisfaction, parental self-efficacy, social support, and cost-effectiveness are predicted to be greater at 13 and 26 weeks post-baseline for participants receiving the *Well-being* program, compared to participants receiving the *Babycare* program.

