#### Primary and Secondary Analyses

All data analyses will be based on the intention-to-treat principle [53]. Continuous outcomes (eg, measures of perinatal distress, quality of life, couple relationship satisfaction) will be analyzed using general linear mixed models, and multilevel modelling will be used for nested data, to deal with any missing data.

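### The powered Time x Condition interaction gives neither direction nor time point, and it loses power that routine adjustment for the baseline score would recover

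*Protocol article*

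**What the plan says.** All references are to the protocol article.

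- **Sample Size:** "A total of 240 couples (120 couples per group) will be recruited". The text continues: "A sample size of 240 will give a power of .80 for detecting a significant" interaction of time with condition at P<.05, "over three occasions of measurement, with a small effect size of f=0.082". No correlation between occasions is given.
- **Hypotheses:** Well-being participants, compared with Babycare participants, "will show lower levels of distress and a higher level of quality of life at 13 and 26 weeks post-baseline". This is a difference in a stated direction at two named times.
- **Follow-Up Assessments:** "Follow-up assessments will be at 13 and 26 weeks post-baseline". The third occasion is therefore baseline, which Study Design places before randomisation.
- **Descriptive Analyses:** the arms are compared at baseline by significance tests, and later analyses control for whatever differences those tests find.
- **Primary and Secondary Analyses:** "Continuous outcomes (eg, measures of perinatal distress, quality of life, couple relationship satisfaction) will be analyzed using general linear mixed models". The section names no contrast and does not say how the baseline score enters the model.

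**The concern.** The interaction is the only test of effect that the article ties to a significance level. It asks whether the arm difference changes anywhere across baseline, 13 and 26 weeks. A significant result is as likely for harm as for benefit of the same size, and as likely for an effect confined to one visit as for an equal effect at both. The hypothesis is about direction and timing, so estimates at each follow-up are needed to speak to it.

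The second issue is efficiency. Baseline precedes randomisation, so the expected arm difference there is zero. The interaction nevertheless treats baseline as one more outcome and estimates that difference. The rule in Descriptive Analyses does not repair this. Under randomisation any baseline difference is chance, so a rule triggered by a significant test will usually leave the baseline score out of the model. That discards its main value, which is to reduce residual variance. A real benefit is then more easily missed than the collected data require.

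**Working it through.** **Inputs from the article:** N = 240 couples, 120 per arm; three occasions (m = 3); two arms (k = 2); f = 0.082; alpha .05; stated power .80.

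**Assumptions not in the article:** correlation rho between any two occasions, with compound symmetry; equal SDs; one observation per couple; no loss; two-sided tests.

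**1. Reproduce the stated power.**

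For the interaction, lambda = f² x N x m / (1 - rho), with df1 = (k-1)(m-1) = 2 and df2 = (N-k)(m-1) = 476.

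At rho = 0.5: lambda = 0.006724 x 240 x 3 / 0.5 = 9.68, power 0.799. The stated .80 is reproduced. Other correlations do not reproduce it: 0.3 gives .65, 0.4 gives .72, 0.6 gives .88 and 0.7 gives .96.

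**2. Turn f into arm differences, in SD units.**

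f² is one quarter of the variance, over the three occasions, of the arm difference.

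- Sustained (0, d, d) or one visit only (0, 0, d): variance is 2d²/9, so d² = 18 x 0.006724 = 0.1210 and d = 0.348.
- Rising (0, d/2, d): variance is d²/6, so d² = 24 x 0.006724 = 0.1614 and d = 0.402.

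By construction the interaction has lambda 9.68 and power .80 for each pattern.

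**3. Joint 2-df test of the two follow-up differences, adjusted for baseline.**

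After adjustment each follow-up score has variance 1 - rho² = 0.75, and the covariance between them is rho - rho² = 0.25. The inverse of that matrix has 1.5 on the diagonal and -0.5 off it. With 120 per arm the multiplier is 120/2 = 60.

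| Pattern | Noncentrality | Adjusted joint test | Interaction |
|---|---|---|---|
| Sustained | 60 x 2 x 0.1210 = 14.52 | .94 | .80 |
| Rising | 60 x 1.375 x 0.1614 = 13.31 | .91 | .80 |
| One visit only | 60 x 1.5 x 0.1210 = 10.89 | .85 | .80 |

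The degrees of freedom are kept at 2 and 476. The gain therefore comes from using baseline as a covariate and not from dropping a degree of freedom.

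**4. Range over the unstated correlation.**

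For each rho, f was rescaled so that the interaction keeps power .80. For rho from 0.3 to 0.7 the adjusted joint test has power .98 to .88 (sustained), .96 to .87 (rising) and .88 to .82 (one visit only). All exceed .80.

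**5. The averaged contrast.**

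For the mean of the two follow-ups, adjusted for baseline, the residual variance is (1 + rho)/2 - rho² = 0.50, so SE = sqrt(4 x 0.50 / 240) = 0.0913.

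- Sustained: 0.348 / 0.0913 = 3.81, power .97.
- Rising: mean difference 0.75 x 0.402 = 0.301; 0.301 / 0.0913 = 3.30, power .91.
- One visit only: mean difference 0.174; 0.174 / 0.0913 = 1.91, power .48.

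The average does best for a sustained effect and much worse than the interaction when only one visit is affected.

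**The case against.** **The interaction does test the hypothesis.** A reader might infer that the powered test misses the hypothesis altogether. The article does not support that. Because baseline precedes randomisation, the interaction null is the same as no arm difference at 13 and at 26 weeks, which is the hypothesis's global null. Only direction and timing are left open. A two-sided averaged contrast would not settle the timing either, since a large effect at one visit can make it significant.

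**The article does not make the interaction the criterion of success.** This stands. Sample Size gives a basis for power, while the analysis section says only that continuous outcomes "will be analyzed using general linear mixed models, and multilevel modelling will be used for nested data". That wording is compatible with the analysis recommended here, and a statistical analysis plan that is not shown may name the contrast. Silence about the contrast is therefore not the point. The point rests on two things the article does state: the interaction as the power basis, and baseline adjustment that depends on a test.

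**Replacing the interaction by an average is a trade.** This also stands. The average falls from .97 to .48 if the effect is at one visit only, which is no small cost. What improves power in every pattern tried is the baseline adjustment.

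**The trial is not underpowered by this.** Correct. Powering on an interaction and then fitting a mixed model is defensible, and no bias follows from it.

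**Conclusion.** The point holds as one of efficiency and of fit between test and hypothesis. The powered test leaves direction and time point open. At the plan's own sample size it has .80 power where a baseline-adjusted joint test of the same two differences has .94, .91 or .85, depending on the shape of the effect. The exact figures rest on an assumed correlation of 0.5, compound symmetry, one observation per couple and no loss. The advantage persists at every correlation from 0.3 to 0.7. The figures are not the power of a full model with both parents in it.

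A reader might infer that the stated .80 is wrong or that more couples are needed. Neither follows: the .80 reproduces under a conventional correlation, and 240 couples give the adjusted test more power than was planned.

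**What to change.** In Sample Size and in Primary and Secondary Analyses, state that each primary outcome is analysed with a mixed model that:

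- always includes the baseline score as a covariate, or constrains the arms' baseline means to be equal;
- accounts for the couple;
- estimates the arm differences at 13 and 26 weeks, each with a 95% CI.

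This replaces the unadjusted interaction, and for the baseline score it replaces the rule in Descriptive Analyses that adjusts only when a difference is detected. State the correlation assumed in the power calculation.

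The average over both visits may be named as the primary contrast, because the hypothesis predicts an effect at both. If so, state its cost: under the assumptions above, power .97 for a sustained effect but about .48 if the effect is at one visit only. If the sponsor does not want to rely on the shape of the effect, the adjusted joint test is the safer choice.

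The change is wording only, uses data already collected and leaves the sample size alone. It should be fixed before outcome data are examined. If a separate analysis plan already names such a contrast, the Sample Size text should be aligned with it.
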